## Abstract

**Background:**

Neurocognitive disorders are an important societal challenge and the need for early prevention is increasingly recognized. Meta-analyses show beneficial effects of cognitive activities on cognition. However, high financial costs, low intrinsic motivation, logistic challenges of group-based activities, or the need to operate digital devices prevent their widespread application in clinical practice. Solving jigsaw puzzles is a cognitive activity without these hindering characteristics, but cognitive effects have not been investigated yet. With this study, we aim to evaluate the effect of solving jigsaw puzzles on visuospatial cognition, daily functioning, and psychological outcomes.

**Methods:**

The pre-posttest, assessor-blinded study will include 100 cognitively healthy adults 50 years of age or older, who will be randomly assigned to a jigsaw puzzle group or a cognitive health counseling group. Within the 5-week intervention period, participants in the jigsaw puzzle group will engage in 30 days of solving jigsaw puzzles for at least 1 h per day and additionally receive cognitive health counseling. The cognitive health counseling group will receive the same counseling intervention but no jigsaw puzzles. The primary outcome, global visuospatial cognition, will depict the average of the *z*-standardized performance scores in visuospatial tests of perception, constructional praxis, mental rotation, processing speed, flexibility, working memory, reasoning, and episodic memory. As secondary outcomes, we will assess the eight cognitive abilities, objective and subjective visuospatial daily functioning, psychological well-being, general self-efficacy, and perceived stress. The primary data analysis will be based on mixed-effects models in an intention-to-treat approach.

**Discussion:**

Solving jigsaw puzzles is a low-cost, intrinsically motivating, cognitive leisure activity, which can be executed alone or with others and without the need to operate a digital device. In the case of positive results, these characteristics allow an easy implementation of solving jigsaw puzzles in clinical practice as a way to improve visuospatial functioning. Whether cognitive impairment and loss of independence in everyday functioning might be prevented or delayed in the long run has to be examined in future studies.

**Trial registration:**

ClinicalTrials.gov, NCT02667314. Registered on 27 January 2016.

**Electronic supplementary material:**

The online version of this article (doi:10.1186/s13063-017-2151-9) contains supplementary material, which is available to authorized users.

## Background

Neurocognitive disorders such as mild cognitive impairment and dementia become increasingly important healthcare issues [1]. Engagement in cognitively challenging activities is associated with a reduced risk for future cognitive impairment [2] and dementia [3]. It is among the factors with the highest projected impact on the prevalence of Alzheimer’s dementia [4]. Randomized controlled trials show beneficial cognitive effects of diverse cognitive activities such as cognitive training [5–9], video games [10–13], card and board games [14, 15], and educational programs such as computer, digital photography, or theater courses [16–18]. However, these evidence-based cognitive activities are characterized by obstacles such as high financial costs, low intrinsic motivation, logistic challenges of group-based activities, or the need to use digital devices. We believe that these characteristics of currently investigated cognitive activities reduce their feasibility and implementation in clinical practice.

Solving jigsaw puzzles is a cognitively challenging activity, especially within the visuospatial cognitive domain. We assume that visuospatial cognitive demands comprise perception, constructional praxis, mental rotation, processing speed, flexibility, working memory, reasoning, and episodic memory. In contrast to other cognitive activities, mentioned above, it depicts a low-cost, intrinsically motivating leisure activity which can be executed alone or with others and without the need to operate digital devices. However, to our knowledge, the effect of solving jigsaw puzzles on cognition has not been investigated yet. Next to the positive impact of a wide range of cognitively challenging activities on cognition, several other findings indicate the potential of jigsaw puzzles to promote visuospatial cognitive health. Performance in solving jigsaw puzzles is highly correlated with performance in visuospatial reasoning tasks [19]; jigsaw puzzle play in preschoolers is associated with future visuospatial transformation skills [20]; and engagement in intellectual activities including jigsaw puzzles predicts a reduced risk of Alzheimer’s dementia [21–23]. Thus, the primary aim of this study is to evaluate the effect of solving jigsaw puzzles on visuospatial cognition.

Furthermore, the effects of cognitive interventions on daily functioning and psychological outcomes are scarcely investigated [24–26]. As secondary aims, this study thus examines the effects of solving jigsaw puzzles on visuospatial everyday functioning such as instrumental activities of daily living and self-reported cognitive failures, and on psychological outcomes such as well-being, general self-efficacy, and perceived stress.

## Methods

The Jigsaw *P*uzzles *A*s *C*ognitive *E*nrichment (PACE) study will take place at Ulm University, Germany, as a randomized, active-controlled, assessor-blinded superiority trial with two parallel groups. Between March and approximately October 2016, we will include and randomly assign 100 cognitively healthy, middle-aged and older adults (age 50 years and above) to a jigsaw puzzle group or a cognitive health counseling group with a 1:1 allocation ratio in blocks of four, stratified by cognitive status and age. Participants in the jigsaw puzzle group will engage in 30 days of solving jigsaw puzzles (6 days/week over a period of 5 weeks for at least 1 h/day) and receive cognitive health counseling (15-minutes face-to-face counseling plus three telephone calls). The cognitive health counseling group will receive the same counseling intervention but will not solve any jigsaw puzzles during the intervention period. The SPIRIT 2013 Checklist provides an overview about the contents of this study protocol (see Additional file 1).

### Procedure

The Ethics Committee of Ulm University approved this study. We will invite individuals interested in participating in the study to a telephone-based interview. Here, they will receive detailed study information and give oral informed consent. A pre-screening will assess eligibility (t_1_, see Figs. 1 and 2). At an appointment at Ulm University, successfully pre-screened participants will be able to give written informed consent and will undergo further screening (t_2A_). For included participants, the procedure will consist of a 1.5-h pretest assessment composed of neuropsychological tests and questionnaires (t_2B_) followed by the face-to-face cognitive health counseling (t_2C_). Subsequently, non-blinded study staff will disclose the group allocation to the participants (t_2D_). Within 2 weeks after the baseline assessment, the 5-week intervention period will start. We will contact all participants three times via telephone for cognitive health counseling and the assessment of adverse events (AEs, t_3_ – t_5_). These telephone-based interviews will also serve to monitor the jigsaw puzzle experience and protocol adherence in the jigsaw puzzle group. Within 2 weeks after the intervention period, we will assess the same outcomes as in the pretest assessments in the 1.5-h posttest assessment at Ulm University (t_6_). Psychologists who are blind to group allocation will conduct the pretest and posttest assessments.

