### Participants

The study aims to include 100 participants who we will recruit via local newspaper articles and flyers. Inclusion criteria are 50 years of age or older, unimpaired cognition defined by a Mini-Mental State Examination (MMSE) [27] score ≥ 24, the commitment to invest at least 1 h per day for 30 days in solving jigsaw puzzles within a 5-week period, an interest in solving jigsaw puzzles, and low jigsaw puzzle experience in the past 5 years (fewer than five completed jigsaw puzzles).

Exclusion criteria are the participation in another interventional study and self-reported, uncorrected impairment in vision (e.g., red-green color blindness) or motor function of the upper extremity (e.g., hand tremor) that considerably impairs jigsaw puzzle performance. In addition, individuals with any self-reported psychiatric, neurological, or other diseases that could affect cognitive change over time will be excluded. These diseases comprise current major depression, dementia or Parkinson’s disease, a history of stroke with current impairment, epilepsy, multiple sclerosis, or a current malignant tumor. Apart from the cognitive impairment, which we will assess at the on-site screening (t_2A_), telephone-based pre-screening will examine inclusion and exclusion criteria after oral informed consent (t_1_, see Figs. 1 and 2).

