#### Predictive variables of cognitive decline and dementia

The investigators will obtain the predictive socio-demographic variables age, gender, years of education, and main profession, using interview-based questionnaires. Three questions on the subjective degree of jigsaw puzzle experience on a 5-point rating scale (answers range from “very high” to “not at all”), the number of jigsaw puzzle hours, and the number of connected jigsaw puzzle pieces within participants’ lifetime will assess lifetime jigsaw puzzle experience. The assessment of risk factors for cognitive decline and dementia with self-rating questionnaires will include items on high blood pressure, hypercholesterolemia, diabetes mellitus, smoking, alcohol misuse, and obesity. The newly developed Challenging Leisure Activity Questionnaire is based on the CHAMPS Physical Activity Questionnaire for Older Adults [46] and will serve as a measure of the protective factors social, physical, and cognitive activities. Participants will indicate for each of 44 socially, physically, and cognitively challenging activities whether they performed them at least once during the past 4 weeks. A short 14-item Mediterranean diet questionnaire [47] will assess components of a Mediterranean diet. The measurement of risk and protective factors will serve as the basis for individual feedback in the cognitive health counseling and for the assessment of behavior changes between pretest and posttest assessments.

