### Interventions

Participants will be randomly assigned to one of two groups, the jigsaw puzzle group or the cognitive health counseling group (see Fig. 2). The jigsaw puzzle group will receive the 30-day jigsaw puzzle intervention and the cognitive health counseling, while the cognitive health counseling group will receive the cognitive health counseling only. We will ask the participants of the cognitive health counseling group not to solve any jigsaw puzzles within the 5-week intervention period. Participants of the cognitive health counseling group will receive a jigsaw puzzle after completion of the posttest assessments.

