#### Jigsaw puzzle intervention

Participants of the jigsaw puzzle group will solve jigsaw puzzles on 6 days a week for 5 weeks for at least 1 h per day. Every participant will get the same 300 piece jigsaw puzzle at first (*Beautiful Prague* by RSV; piece size: 2.45 × 2.4 cm). The participants will select subsequent puzzles out of a catalogue with 200, 300, 500, 1000, and 1500 piece jigsaw puzzles of the RSV adult puzzle 2016 collection (piece sizes included: 2.8 × 3.0 cm; 2.45 × 2.4 cm; 2.0 × 1.8 cm; 1.9 × 1.7 cm; and 1.8 × 1.7 cm, respectively).

The intervention will take place at participants’ homes. They will protocol their jigsaw puzzle time in a diary immediately after each jigsaw puzzle session. On each jigsaw puzzle day, participants will note the jigsaw puzzle name, the jigsaw puzzle duration, and if necessary additional comments about their experiences. Immediately after each of the three telephone-based cognitive health counseling sessions, participants will report the content of the diary for the monitoring of the protocol adherence and of the jigsaw puzzle performance (time per connected piece). Finally, the telephone-based interview includes questions about participants’ jigsaw puzzle experience for each solved jigsaw. Jigsaw puzzle experience will include the desire to solve the jigsaw puzzle, the pleasure in solving the jigsaw puzzle, the experienced competence of solving the jigsaw puzzle, and the perceived difficulty of the jigsaw puzzle. We will evaluate all four measures with a single question and a 5-point rating scale that ranges from “very high” to “not at all”. Participants will be able to freely choose their preferred jigsaw puzzles. However, we will recommend them to constantly increase the difficulty and challenge of the jigsaw puzzles through the increase of pieces per puzzle - which is accompanied with a decrease in piece size - as long as this does not reduce their pleasure and fun. These recommendations will depend on the reported perceived difficulty, challenge, pleasure, and fun, and their jigsaw puzzle performance (time per connected piece). If participants report adverse conditions associated with solving jigsaw puzzles (e.g., muscle pain during jigsaw puzzling or the development of a strong craving to solve jigsaw puzzles), the study staff will recommend to reduce puzzle time, not to stick to the protocol of at least 1 h per day, or to stop solving jigsaw puzzles as appropriate.

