### Blinding and strategies to deal with expectation and motivation effects

Outcome assessors will be blinded to group allocation of participants. To prevent disclosure of group assignment by participants, we will remind them at the last telephone interview (t_5_) not to bring the solved jigsaw puzzles to the posttest assessment. Second, we will remind them at the last telephone interview (t_5_) and immediately before the posttest assessment (t_6_) not to tell the assessor anything that may give hints to the allocated group. Here, the participants will also sign a confirmation statement that they received this information. Blinding participants to the assigned group is by nature not feasible. Given the lack of a double-blind design, several strategies will serve to reduce potentially different expectations and motivation between groups [49]. First, implementing an additional component in both groups (i.e., cognitive health counseling) aims to induce similar positive expectations regarding cognitive benefits (cf. component control design; [49, 50]). Second, the investigators will tell all participants before disclosure of group assignment that (a) both groups should benefit cognitively from the cognitive health counseling and that (b) it is currently not known whether solving jigsaw puzzles has a positive impact on cognition. Third, participants of both groups will receive the same amount of study staff contact during the intervention period (apart from questions regarding jigsaw puzzle experiences and adherence) and the same opportunities to express their concerns and to receive attention (face-to-face health counseling, three telephone calls, and the possibility to contact the study staff whenever wished). As differential expectations between groups are still likely to some degree and cannot be completely excluded, the study assesses expectations on a continuous and on a categorical scale in the last telephone call approximately 9 days before the follow-up test (see confounding variables section). We avoid an assessment at the follow-up, as this might either influence test performance through activated expectations (when assessed directly before the neuropsychological tests) or might alter expectations according to test performance (when assessed directly after the neuropsychological tests) [49]. In addition, we will aim to keep test motivation high in both groups by asking participants again, directly before the follow up, whether they want to receive their normed individual test results after study completion. One item on a 5-point rating scale at the posttest assessment (t_6_) will assess test motivation.

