### Statistical analysis

The primary efficacy analysis will be based on mixed-effects models' group × time interaction [53] in an intention-to-treat approach [54] that includes all randomly assigned participants with follow-up observations. Effect sizes will include standardized differences in the pretest-posttest change scores between both groups. Standardization will be based on (1) baseline scores and (2) pretest-posttest change scores. In additional analyses, we will account for potential confounding variables such as baseline performance, the number of challenging social, physical, and cognitive activities performed in the past 4 weeks, the pretest-posttest change in these activities, Mediterranean diet in the past 4 weeks, and pre-posttest change in diet, age, education, participants’ test motivation at the posttest assessment, and their expectations of cognitive benefits.

As the primary intention-to-treat analysis is a conservative method, which may underestimate the true effect size of solving jigsaw puzzles for individuals who follow the protocol, we will use a supportive per-protocol analysis, which includes only participants who completed at least 80% of the jigsaw puzzle protocol (≥24 jigsaw puzzle days with a minimum of 45 min). With this supportive analysis, we do not only assess the robustness of effects, but may also receive a more accurate estimate of the true effect size given optimal conditions.

For subgroup and moderator analyses, pre-specified variables comprise baseline global visuospatial cognition, amount of lifetime puzzle experience, number of challenging social, physical, and cognitive activities within the intervention period, age, MMSE, and experienced pleasure in solving jigsaw puzzles.

Finally, we will assess cognitive demands of solving jigsaw puzzles and the transfer potential of gains in jigsaw puzzle skill on gains in the study outcomes by calculating the correlation between jigsaw puzzle skill in the 40-piece puzzle and the study outcomes at baseline.

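### No dedicated check that controls keep to the no-puzzle request is described; adherence monitoring and the per-protocol criterion cover the jigsaw group only

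*Protocol article*

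**What the plan says.** **Eligibility (Participants).** Every participant, future controls included, must have "an interest in solving jigsaw puzzles, and low jigsaw puzzle experience in the past 5 years", and must be ready to puzzle for at least an hour a day on 30 days.

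**Control obligation (Interventions).** "We will ask the participants of the cognitive health counseling group not to solve any jigsaw puzzles within the 5-week intervention period". The opening of Methods states as fact that this group will solve no puzzles during the period. Controls receive a puzzle from the study only after posttest.

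**Adherence monitoring.** Four places treat adherence as a matter for the jigsaw group:

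- Procedure, on the three calls: "These telephone-based interviews will also serve to monitor the jigsaw puzzle experience and protocol adherence in the jigsaw puzzle group".
- Jigsaw puzzle intervention, on the diary kept by that group: "participants will report the content of the diary for the monitoring of the protocol adherence".
- Blinding and strategies to deal with expectation and motivation effects: staff contact is equal "apart from questions regarding jigsaw puzzle experiences and adherence".
- Statistical analysis: the per-protocol analysis "includes only participants who completed at least 80% of the jigsaw puzzle protocol". No criterion for controls is given.

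**Indirect sources that reach controls.**

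- A 44-item leisure activity questionnaire asks of each activity "whether they performed them at least once during the past 4 weeks" and is used for pretest-posttest change. Its items are not listed.
- The second and third counseling calls ask about changes in the predictive factors, which include cognitive activities.
- A timed 40-piece puzzle, described under secondary outcomes, measures jigsaw skill.

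**The concern.** On the control side, abstaining from puzzles is what separates the two groups. The people asked to abstain entered the trial because puzzling interested them, and the counseling tells them that cognitive activity is protective. Some puzzling by controls is therefore foreseeable. The limitations in the Discussion consider a differential effect of the counseling but not this.

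Puzzling by controls makes the two groups more alike and so biases the estimated effect of puzzling towards zero. If its amount is not recorded, a small or null result cannot be set against a known degree of dilution. The per-protocol analysis is meant to approach the effect under good adherence, but it would screen adherence on one side only.

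**Working it through.** **1. The plan's own power figure.** Inputs from the Power analysis section: 50 per group, 15% dropout, f = 0.1, pretest-posttest correlation 0.85, alpha 0.05, stated power 90%.

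- Analysed: 100 × 0.85 = 85.
- Noncentrality for a group × time interaction with two groups and two times: λ = f² × N × 2 / (1 − r) = 0.01 × 85 × 2 / 0.15 = 11.33.
- Power from the noncentral F with 1 and 83 degrees of freedom: 91.4%.

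This agrees with the stated 90%. On the change-score scale the same inputs mean a difference of 4f = 0.40 baseline SD and an SD of change of √(2 × 0.15) = 0.548. A normal approximation with 42.5 per group gives 92.0%.

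**2. Dilution.** Let a share p of controls puzzle enough to gain a fraction e of the full benefit. The contrast is then multiplied by 1 − p × e, and λ by the square of that. The documents give neither p nor e. I take e = 0.5 and let p run from 0 to 30%.

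| p | Contrast multiplier | λ | Power, 85 analysed |
|---|---|---|---|
| 0 | 1.00 | 11.33 | 91.4% |
| 10% | 0.95 | 10.23 | 88.5% |
| 20% | 0.90 | 9.18 | 85.0% |
| 30% | 0.85 | 8.19 | 80.7% |

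A harsher assumption, that 20% of controls gain the full effect (e = 1), gives a multiplier of 0.80, λ = 7.25 and power 75.9%.

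**3. What the indirect sources can show.**

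- *Questionnaire.* Posttest falls within two weeks after the five-week period. A four-week recall taken on the day the period ends reaches back over 4 of the 5 weeks. Taken two weeks later it covers 4 − 2 = 2 of the 5. If jigsaws are an item, the yes/no answer gives a share of controls who puzzled in that window, but no hours.
- *Calls 2 and 3.* The questions concern changes in behavior on the predictive factors generally. Puzzling might be mentioned, but no question about it is described.
- *40-piece test.* Heavy puzzling by controls might show as a gain in skill, but so might simple retest practice.

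At best these sources give a partial view of whether controls puzzled. None says how much. The planned adjusted analyses use the number of challenging activities and its change, not puzzling by controls.

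**The case against.** The strongest reply has three parts.

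*The article is condensed.* Call scripts, questionnaire items and the figures are not shown, and an article commonly leaves exact questions to the full protocol. This stands in part: one can say only that no dedicated check is described. It does not remove the point, because the restriction to the jigsaw group is written out in several sections rather than inferred from silence.

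*Contamination may be small.* Participants had completed fewer than five puzzles in five years, and the study supplies controls with none before posttest. Both facts make heavy puzzling less likely, and p = 30% may be pessimistic. They are reasons to expect little of it, not a way to find out.

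*The consequence is moderate.* With 5% to 15% dilution, power stays at 81% to 89%. The bias is towards zero, so in a superiority trial it does not create a false positive. This stands.

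A reader might go further and infer that the no-puzzle request is never checked, that puzzling by controls cannot be detected, or that a null result would be uninterpretable. The documents do not support this. The questionnaire, the calls and the skill test could each reveal some puzzling, and the assumed dilution leaves most of the contrast. A reader might also see the extra puzzle interview as contradicting the equal-contact strategy. It does not, because the plan names those questions as the exception and also measures expectations and test motivation.

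**Conclusion.** The point holds as a gap in monitoring. Adherence is followed, and the per-protocol criterion defined, for the jigsaw group only. The controls' one restriction rests on a request, with indirect and non-quantitative sources behind it. Puzzling by controls could therefore not be quantified, and any such puzzling would make the effect look smaller than it is.

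A contrast 5% to 15% smaller lowers power from about 91% to between 89% and 81%. That range rests wholly on assumed values of p and e. The power calculation is correct on its own inputs, and the intention-to-treat comparison remains valid as a comparison of the groups as randomised. The gap is worth closing because the remedy is cheap, not because it undermines the trial.

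**What to change.** 1. In the three calls (t3, t4, t5), after the counseling, ask controls one neutrally worded question: hours spent on jigsaw puzzles since the last contact.
2. Have non-blinded staff ask it again at t6, once the outcome measures are complete. They already ask about adverse events at that moment, so assessor blinding is not affected.
3. Report control puzzle hours beside the jigsaw-group hours from the diary.
4. In the supportive per-protocol analysis, exclude controls who puzzled beyond an amount fixed in advance, before outcome data are seen. Because this selects on behavior after randomization, it should remain supportive.

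The primary intention-to-treat analysis, sample size and randomization stay as they are. The cost is a few minutes in contacts that already take place. The small downside is that the question may remind controls of puzzles, which is why it should follow the counseling and be worded neutrally.
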